#### Effectiveness of the more sustained promotion by local authorities

The effectiveness of the more sustained promotion by local authorities will be measured by the numbers of deaths by suicide and suicide attempts considered separately in the 12 months following the start of this form of promotion in the control group.

Table 2 provides a summary of all outcome measures collected by level of availability as well as their timeframe.

If users of the StopBlues program stop connecting to it, they will receive push-up notifications on their smartphones or reminder emails regarding the completion of questionnaires, to improve adherence.

#### Statistical considerations

Characteristics of local authorities and of users of the StopBlues program will be described by the mean and standard deviation (SD) for continuous variables or by number (%) for categorical variables.

To assess the effectiveness of the intervention on the primary outcome (number of suicidal acts at the local authority level), we will compare the number of overall suicidal acts at 12 months and of suicides and suicide attempts separately between the trial arms adjusted on the number observed during the 12 months before the intervention.

We will use a Poisson regression analysis with clusters as analysis units and cluster size as offsets and adjust for baseline data and local authorities’ characteristics (population size, ecological index of deprivation, type of local authorities forming the cluster, etc.). A similar method will be used for all secondary outcomes measured at the level of local authorities.

For secondary outcomes measured on the users of the StopBlues program, mixed-model repeated-measures analyses will be used. This method will enable the inclusion of all users regardless of their level of adherence to the program, which will allow us to carry out the analysis despite some missing values. Adjustments will be made on the initial level of psychological distress of each user and on demographics. By using mixed-model repeated-measures analyses [61], we will also be able to account for potential clustering effects through the incorporation of adequate random effects for local authorities. Transformation of outcome variables will be done as necessary to meet distributional assumptions and to accommodate potential outlying observations. Additional subgroup analyses will be carried out to assess separately the effect of the intervention on users with a history of suicide attempts and those without.

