### Sample size and power

The number of clusters was fixed by the identification of 34 clusters that agreed to be involved in the trial. The proportion of inhabitants who died from suicide or who made suicide attempts over a 12-month period was estimated to be 0.215% (personal data). We used an expected rate of 0.190% in the experimental group, which represents a reduction of 11.6%, slightly higher than the 10% global target supported by WHO for interventions on suicide [10]. In a two-arm, individually randomized trial, this would lead to a required number of participants of 1,229,350 to achieve a power of 80% with a Type I error rate of 2.5%. Type I error is set at 2.5% because two experimental groups are compared to the control group. Clustering also has to be taken into account. As the number of voluntary clusters was fixed, we calculated what the intraclass correlation coefficient (ICC) would be in order to achieve a power of 80% with our pre-specified number of clusters. Although we acknowledge that such an approach is not classical, it enables us to take into account feasibility reasons. Our mean cluster size equals 138,172 inhabitants and, therefore, randomizing 11 clusters in each arm allows for achieving 80% power if the ICC is around 10^−5^. Although this is a very low ICC, one has to keep in mind that clusters are geographical areas and ICCs are known to be lower in large clusters as compared to small ones. Moreover, ICC is known to depend on prevalence [37], with small ICC values for prevalence close to 0 or 1, and we expect very low rates (about 0.2%). As a consequence, we considered that a 10^−5^ ICC value would be appropriate in our trial.

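### The sample size assumes between-cluster variation (design effect about 2.4), but the Poisson model named for the primary outcome states no allowance for it, so as written each 2.5% test is anti-conservative

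*Protocol article*

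**What the plan says.** All references are to the protocol article.

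**Sample size and power.** The section says "Clustering also has to be taken into account". It starts from an individually randomised two-arm comparison of 0.215% with 0.190%, giving a "required number of participants of 1,229,350 to achieve a power of 80% with a Type I error rate of 2.5"%. It then finds the intraclass correlation at which 11 clusters per arm still give 80% power, and settles on about 10^-5. It also says "Our mean cluster size equals 138,172 inhabitants". On multiplicity: "Type I error is set at 2.5% because two experimental groups are compared to the control group".

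**Statistical considerations.** The primary analysis is given as "We will use a Poisson regression analysis with clusters as analysis units and cluster size as offsets and adjust for baseline data", with further adjustment for population size, a deprivation index and type of local authority. The comparison is described as "adjusted on the number observed during the 12 months before the intervention". A similar method is to serve every other outcome measured at local-authority level. For outcomes in users of the program, the same section says that clustering will be handled by random effects for local authorities. It says nothing comparable for the primary outcome.

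**The concern.** The two sections carry different variances for the same counts. The design allows for real differences in suicidal-act rates between areas. The named analysis attributes all residual variation to Poisson chance.

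Taking clusters as the units does not remove the problem. In a Poisson model the standard error of an arm's log rate depends only on its total number of events, so 11 aggregated counts give the same standard error as treating every inhabitant as independent.

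At stake is the validity of the primary test. The significance level was halved to 2.5% to protect two comparisons with control, and an understated standard error more than undoes that protection. A false benefit could support the wider delivery foreseen in the Discussion. A false increase in suicidal acts could feed the decision to stop described under Ethical considerations.

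**Working it through.** **Inputs from Sample size and power:** rates 0.215% and 0.190%; type I error 2.5% per comparison; power 80%; mean cluster size m = 138,172; 11 clusters per arm; intraclass correlation (ICC) about 10^-5.

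**Assumptions, not in the article:** correlation r between a cluster's true rates in the two years, 0.5 to 1.0; coefficient of variation (CV) of cluster size, 0 to 0.7.

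**1. Reproduce the plan's figures.** The two-proportion formula at two-sided 2.5% and 80% power gives 614,678 per arm, 1,229,356 in total, against 1,229,350 stated. One-sided 2.5% gives 1,015,154 and does not fit, so the tests are taken as two-sided. The design effect that 11 clusters per arm can carry is 2 × 11 × 138,172 / 1,229,350 = 2.473, which means ICC = 1.473 / 138,171 = 1.07 × 10^-5. The plan's value of about 10^-5 is confirmed.

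**2. Variance the plan assumes.** Design effect = 1 + (138,172 − 1) × 10^-5 = 2.38. Expected acts per cluster = 138,172 × 0.00215 = 297. Between-cluster CV of rates = √(10^-5 × 0.99785 / 0.00215) = 6.8%.

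**3. Standard errors under the null.** Each arm expects 11 × 297 = 3,268 acts. The Poisson model reports a standard error for the log rate ratio of √(2 / 3,268) = 0.025. The plan's own ICC gives 0.0247 × √2.38 = 0.038.

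**4. Type I error, covariates explaining nothing, equal sizes.** 2 × (1 − Φ(2.241 / √2.38)) = 2 × (1 − Φ(1.452)) = 14.6% per test. At ICC 1.07 × 10^-5 it is 15.4%.

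**5. With the planned baseline adjustment, equal sizes.** The baseline count is itself noisy. Its reliability is 1.38 / 2.38 = 0.58, so it can explain at most a share r² × 0.58 of the between-cluster variance. The residual design effect is D = 1 + 1.38 × (1 − 0.58 r²), and the error is 2 × (1 − Φ(2.241 / √D)).

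| r | D | Type I error, formula | Type I error, simulated |
|---|---|---|---|
| 0.5 | 2.18 | 12.9% | about 13% |
| 0.8 | 1.87 | 10.1% | about 10% |
| 1.0 | 1.58 | 7.5% | about 7% |

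The simulation used 34 clusters in three arms with log-normal cluster rates matching ICC 10^-5, 4,000 trials per scenario. With ICC set to 0 and equal sizes it returned about 2.5%, as it should.

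**6. Unequal sizes, simulated, size CV 0.7.** About 18% unadjusted. With baseline adjustment, about 16% at r = 0.5, 12% at r = 0.8 and 8% at r = 1.0.

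**7. At least one false rejection over the two tests, equal sizes, simulated.** About 25% unadjusted, and 13 to 22% with baseline adjustment at r = 1.0 to 0.5.

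**8. After the fix.** Quasi-Poisson with a t reference gave 2.3 to 2.9% per test with equal sizes, and 2.6 to 4.0% with size CV 0.7.

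**9. Power.** With equal sizes and a normal reference, power is 81.6% at ICC 10^-5 and 80.0% at 1.07 × 10^-5. A t reference costs a little. The standardised effect is 3.14 and the critical value at 31 degrees of freedom is 2.36, so power without covariates is about Φ(3.14 − 2.36) = 78%. Baseline adjustment at r = 0.5 returns this: 3.14 × √(2.38 / 2.18) = 3.28, and Φ(3.28 − 2.36) = 82%.

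**The case against.** The best defence is that the article names a model family and does not say that the model is unscaled. It excludes neither a dispersion parameter nor a robust variance nor a random effect. A condensed article may leave variance estimation to an analysis plan, which is not shown here, and the sample-size section shows that the authors know clustering matters. This stands in part: a reader might infer that the trial will certainly be analysed without any correction, and the article does not establish that. It does not remove the point. The stated model conflicts with the stated design assumption, and the same section takes care to name random effects for user-level outcomes while naming nothing for the primary one.

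A second objection is that the planned covariates absorb part of the variation. This also stands. A reader might infer a flat error rate of 12 to 17%, but such a figure ignores the adjustment that the quoted sentence itself makes. Deprivation and type of authority could lower the error further if they explain much; the article gives no basis for saying how much. Baseline alone cannot close the gap, because a count of about 297 acts is too noisy even when true rates are perfectly stable.

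Two further inferences are not supported:

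- **Larger error rates from a between-cluster CV of 10 to 15%.** These would need an ICC of about 2.2 × 10^-5 to 4.8 × 10^-5, two to five times the plan's value.
- **A large loss of precision from entering the baseline as a raw count.** The section fixes no functional form for the baseline, and population size is in the model as well. With population included and r = 0.8, using the log rate cut the variance of the arm effect by only about 0 to 13% in simulation. That is a matter of efficiency, not validity.

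Repeat acts by one person could add variation, but the article gives no figure for them and nothing here rests on them.

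**Conclusion.** Wrong as written. The plan assumes variance about 2.4 times Poisson, and the primary model it names has variance equal to the mean. At the plan's own ICC the 2.5% tests were anti-conservative in every scenario examined:

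- about 15% if covariates explain nothing and clusters are equal in size;
- about 7 to 16% with baseline adjustment, for r from 0.5 to 1.0 and size CV from 0 to 0.7;
- up to about 18% unadjusted with size CV 0.7.

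The direction follows from the document alone. The exact size rests on r, the CV of cluster size and the share explained by the other covariates, none of which the article reports. If the unseen analysis plan already estimates overdispersion, the error is confined to the article's wording and should be corrected there.

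**What to change.** State in Statistical considerations, and in the analysis plan, that the cluster-level model for the primary outcome and for all cluster-level secondary outcomes estimates extra-Poisson variation between clusters and uses small-sample inference. Quasi-Poisson regression with the log-population offset and a t reference on residual degrees of freedom is one way, and the one checked above. Another model with a between-cluster variance term would serve if its small-sample behaviour is shown. The planned covariates can stay.

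The cost is one or two sentences and wider confidence intervals. No clusters need to be added. Under the equal-size assumption of the sample-size section, power remains about 80%. With very unequal cluster sizes the corrected test may stay slightly above 2.5% (up to about 4% at size CV 0.7), which is worth checking against the actual cluster sizes.

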#### Secondary objectives

The secondary objectives will be measured both at the cluster level (geographical area sharing a common authority) and among users of the StopBlues program.

Secondary objectives considered at the cluster level are as follows:
To assess the cost-effectiveness and to run a budgetary impact analysis of the intervention

Secondary objectives measured among users of the StopBlues program are as follows:
2.To assess the effectiveness of the intervention in terms of the intensity of the utilization of the program3.To assess the effectiveness of the intervention for help-seeking behaviors and participation in supportive activities (any activity that a user finds beneficial for their mental health)4.To assess the effectiveness of the intervention for the evolution of the level of psychological impairment

It should be noted that an additional form of promotion (more sustained promotion by local authorities, described below) will be implemented after 12 months in the control group and evaluated using the same primary outcome measure. In parallel, the long-term effectiveness of the two main types of local promotion (with or without a passive involvement of GPs through their waiting room) will also be assessed.

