### Intervention to be evaluated

The intervention evaluated corresponds to the tailored local promotion of the StopBlues program. Its description below complies with the Template for Intervention Description and Replication (TIDieR) Checklist for intervention description [38].

The StopBlues program will be promoted by the French local authorities participating in the trial. A basic communication toolkit, including a promotion guide, posters, leaflets and key communications messages, will be provided to each local authority at the beginning of the intervention. In addition, a contact person from the municipal staff already involved in health prevention will be appointed in each local authority. They will be in charge of coordinating the promotion of the StopBlues program at the local level and will participate in a day-long training session prior to the beginning of the promotion campaign. Local authorities will then be in charge of promoting the program by choosing their usual municipal communication medium (local newspapers, bulletins and billboards, posters in local shops and bus stops, etc.), by involving local actors of their choice and by developing additional promotion tools if they wish. They will, therefore, be able to develop a tailored intervention adapted to their local context.

Additional promotion of the StopBlues program (intensified promotion) will be carried out in several local authorities by the additional involvement of local GPs. As GPs’ workload is significant in France, due to the fact that they have been put at the heart of care coordination [39], a passive involvement of GPs in the promotion of the StopBlues program was designed. They will receive communication tools on the StopBlues program, such as leaflets or posters, to put in their waiting rooms in order to inform patients and their relatives about the existence of the program.

Finally, the local authorities of the control group will be offered a more sustained promotion at 12 months, which is not part of the main intervention but will also be evaluated during the trial. This promotion will consist of the same promotion as in the basic promotion group to which will be added regular support from the research team with stronger contacts and technical and financial resources for local authorities to implement the promotion and print the tools (flyers, posters, etc.). The inclusion of GPs in this promotion process will be left to local authorities’ discretion.

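### Length of use, safety-plan completion, help-seeking and psychological impairment are assessed only among people who became users, which promotion is designed to influence, so the implied arm comparisons are not protected by randomisation

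*Protocol article*

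**What the plan says.** Under Intervention to be evaluated, the protocol article is explicit about what is randomised: "The intervention evaluated corresponds to the tailored local promotion of the StopBlues program". The app and website are not randomised. Recruitment and eligibility says they are open to residents of every participating local authority.

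Secondary objectives introduces three of its objectives with "Secondary objectives measured among users of the StopBlues program are as follows". They are:
- objective 2: "To assess the effectiveness of the intervention in terms of the intensity of the utilization of the program"
- objective 3: "To assess the effectiveness of the intervention for help-seeking behaviors and participation in supportive activities"
- objective 4: "To assess the effectiveness of the intervention for the evolution of the level of psychological impairment"

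For analysis, Statistical considerations says "For secondary outcomes measured on the users of the StopBlues program, mixed-model repeated-measures analyses will be used", with random effects for local authorities, and then "Adjustments will be made on the initial level of psychological distress of each user and on demographics". Table 2 and the section on psychological impairment place the initial distress score (GHQ-12) at the user's first connection, T0. They also restrict PHQ-9 and GAD-7 to users whose GHQ-12 suggests distress, and the MINI suicidality module to users with poor PHQ-9, GAD-7 or mood-tracking scores. The Blinding section shows that app data come only from users who consent.

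**The concern.** The Background says promotion is needed so that people know such programs exist and are encouraged to use them. Arm therefore affects who becomes a user, as well as how many do. A control-arm user, with no local campaign in the first 12 months, may differ from someone reached by a poster or a waiting-room leaflet in motivation, severity or existing care. Comparing users by arm conditions on a consequence of allocation, so the groups compared are no longer those that randomisation made comparable.

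At stake is what the trial may conclude. A campaign that succeeds in reaching less motivated people could appear to worsen distress or shorten use. One that draws in people already ready to seek help could appear to improve both. The SF-12 collected from users is also meant to inform the utility measure for the economic evaluation, so a biased contrast could carry over there.

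**Working it through.** The article gives no expected number of users, user profile by arm or effect size for these outcomes, so there is no planned figure to reproduce. The point is structural, and is checked against the text and then illustrated.

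**1. The chain in the text**
- Randomised factor: promotion (Intervention to be evaluated).
- Availability of the app: all arms (Recruitment and eligibility).
- Purpose of promotion: awareness and use (Background).
- Source of user-level data: consenting users only (Blinding).
- Claim: effectiveness of the intervention, measured among users (Secondary objectives).

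Registration therefore lies between allocation and every user-level outcome.

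**2. What the planned method handles**
- Mixed model: missing follow-up among people who are already users.
- Random effects for local authorities: clustering.
- Adjustment for initial distress and demographics: the part of selection that those variables measure.
- None of the three: unmeasured differences in who registers.

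**3. Outcomes that escape the problem**
- Suicidal acts come from administrative databases covering all residents by zip code.
- Downloads and connections are counted for each participating zip code (Table 1), so they can be set against the whole cluster population. Table 2 nevertheless lists them under users.

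**4. Illustration (all inputs assumed, none from the documents; true effect of promotion on anyone's outcome = 0)**

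B is baseline distress and U an unmeasured trait such as motivation, both independent standard normal in residents. The outcome is Y = 0.5B - 0.3U + 0.8e, with e standard normal and higher meaning worse. Its SD in residents is sqrt(0.25 + 0.09 + 0.64) = 0.99. Registration follows logit(p) = b0 + bB·B + bU·U, which gives uptake of about 0.3% to 1%. Y is regressed on arm and B among registrants. Each result is the mean of 30 runs of 2 million residents per arm, with Monte Carlo standard errors of 0.002 to 0.003.

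| Scenario | Control (b0, bB, bU) | Promotion (b0, bB, bU) | Adjusted arm difference |
|---|---|---|---|
| A: control users more motivated | -6.5, 0.8, 1.0 | -5, 0.5, 0.3 | +0.21 (spurious harm) |
| B: promotion users more motivated | -6, 0.8, 0.3 | -5.5, 0.5, 1.0 | -0.20 (spurious benefit) |
| C: same selection, same rate | -6, 0.8, 0.3 | -6, 0.8, 0.3 | 0.00 |
| D: same selection, higher rate | -6, 0.8, 0.3 | -5, 0.8, 0.3 | 0.00 |

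Check by hand: when uptake is rare, the mean of U among registrants is close to bU, so the bias is close to -0.3 × (bU in promotion - bU in control).
- A: -0.3 × (0.3 - 1.0) = +0.21.
- B: -0.3 × (1.0 - 0.3) = -0.21, against -0.20 simulated.
- C and D: -0.3 × (0.3 - 0.3) = 0.

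The number of users does not enter this expression, so more users would not shrink the bias. A different number of users per arm does not create it either (D). It arises when the type of user differs.

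**The case against.** **Arm comparison not written down.** Statistical considerations mentions comparing trial arms only for the primary outcome. A within-user analysis is a possible reading. This stands as a point of wording. But the Abstract states these objectives as effectiveness of the promotion, and the outcomes section speaks of the intervention's effect on users' impairment. With promotion as the intervention, that calls for an arm contrast. Change within users alone would not estimate the effect of promotion either.

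**Selection can be partly described.** Discovery channel and help-seeking are recorded at T0, and subgroups by history of suicide attempts are planned. This stands: these data allow the user groups to be profiled and some selection adjusted for. They do not restore a randomised comparison.

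**Not every use measure is affected.** This also stands. A reader might infer that all comparisons of use are compromised, but the zip-code count keeps the randomised comparison if analysed over cluster populations.

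**Size.** A reader might take the illustration as an estimate of bias in this trial. The documents do not support that, since the inputs are assumed and scenarios C and D show zero bias when selection is alike across arms.

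**Model type.** A reader might also object that a repeated-measures model does not suit counts, binary outcomes or values recorded once. The model for each outcome is normally left to the analysis plan, which is not shown, so nothing is claimed on that.

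**Conclusion.** The concern holds for length of use, safety-plan proportion, help-seeking, psychological impairment and SF-12 among users. Arm comparisons on these are observational within a randomised trial, and the article does not say so. Bias in either direction is possible if the kind of person who registers differs by arm. Neither its presence nor its size can be established from the documents.

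A reader might infer that the trial's main result is undermined. It is not, because the primary outcome covers all residents whether or not they use the app. Only secondary conclusions are at issue, and the remedy lies in analysis and wording. The point should be fixed before these results are reported as effects of the intervention, but it does not call the design into question.

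**What to change.** 1. In Statistical considerations, make the randomised comparison of use on cluster populations: downloads or registrations, users still active at a stated time, and completed safety plans, each per resident. Use the cluster-level count model with population offset already planned for local-authority outcomes, and interpret the results as uptake or reach. State that the zip-code count of downloads and connections belongs here.
2. Label the user-level mixed models of help-seeking, GHQ-12, PHQ-9, GAD-7, MINI and SF-12 as non-randomised and exploratory. Show users' T0 profile by arm (distress, discovery channel, help-seeking) and add a sensitivity analysis for selection into use.
3. Reword objectives 3 and 4 so that they do not claim a randomised effect of the intervention.
4. Do not present users reporting help-seeking per resident as an effect on help-seeking. Non-users supply no such data, so the rate would rise with registrations alone.

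Cost: wording and analysis text only. The app data are already planned for collection, and cluster populations are already needed for the offset. The price is giving up causal claims about users' symptoms, quality of life and help-seeking.

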## Methods/design

### Study design

This study will be implemented as a three-arm, parallel-group, cluster-randomized controlled superiority trial, with before-and-after observation. Cluster-randomization was deemed mandatory because of potential contamination issues. Indeed, the very nature of the intervention assessed (i.e., a promotion program) cannot be applied at the individual level. This is typically a cluster-cluster intervention, as defined by Eldridge et al. [32]. Clusters were defined as geographical areas sharing a common local authority. These local authorities can either be cities or a grouping of cities (“*communautés de communes*” or “*communautés d’agglomérations*”) based on the local health governance of each area. If several adjacent local authorities volunteer individually to participate in the trial, they will be considered as a unique local authority.

Clusters will be randomly assigned to one of the following three arms with a ratio of 1:1:1:
Arm 1: no promotion of the StopBlues program (*control group*)Arm 2: promotion of the StopBlues program by local authorities only (*basic promotion group*)Arm 3: promotion of the StopBlues program by local authorities with an additional passive involvement of GPs through their waiting rooms (*intensified promotion group*)

The initial trial duration will be of 12 months. Baseline data on the number of suicidal acts, collected 12 months prior to the intervention, will also be considered in each cluster. After a 12-month post-randomization period, clusters from the control group will be allowed for a further 12-month period to launch their promotional campaign supported by the research team through regular contacts and additional technical and financial resources in comparison to arms 2 and 3 (*more sustained promotion by local authorities*). This will facilitate the recruitment of clusters as well as their adherence to the intervention during the first 12-month period [33]. It will also enable us to determine whether promotion led by local authorities could be improved by supporting them in the provision of additional promotional resources.

A complete description of the different steps of the trial is presented in Fig. 1 using the Timeline cluster tool of Caille et al. [34].

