Level of a relative’s depression (for users coming for a relative and not for themselves)	MADRS	X							
Level of health-related quality of life	SF-12	X		X	X	X	X	X	X
Help-seeking behaviors and participation in supportive activities	Ad hoc questionnaire adapted from the General Help-seeking Questionnaire (GHSQ)	X		X	X	X	X	X	X

*GAD-7* 7-item General Anxiety Disorder, *GHQ-12* 12-item General Health Questionnaire, *MADRS* Montgomery-Asberg Depression Scale*, PHQ-9* 9-item Patient Health Questionnaire*, SF-12* 12-item Short Form health survey

^a^M0, M1, etc. refer to the time-lapse in month to the launch of the intervention while T0, T1, etc. refer to the time-lapse in month to the first connection of the user to the StopBlues program

^b^T0’ corresponds to the first time that the MINI suicidality module is submitted to the user (this only happens if the user has a bad score at the PHQ-9 and/or at the GAD-7 and/or for the Likert scales of the mood-tracking system which are not used in the evaluation) so T0’ can, therefore, differ from T0. In the case of the level of suicidal risk, T1, T2, T3, T6, T12 and T24, therefore, corresponds to the time after T0’ and not T0

^c^Depression and anxiety will be measured if the GHQ-12 score suggests potential psychological distress

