## Trial status

The protocol reported here corresponds to the version of 1 September 2018. The intervention of the PRINTEMPS study was launched in April 2018 and the recruitment of potential users of the StopBlues program is taking place until March 2020.

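### User-level contrasts with control have no calendar cut-off, so they mix in control-area data collected after promotion is offered there at month 12

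*Protocol article*

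**What the plan says.** Four statements in the protocol article have to be read together.

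- **Clock.** Table 2, footnote a, says that "T0, T1, etc. refer to the time-lapse in month to the first connection of the user to the StopBlues program"; M times run from launch. The GHQ-12, PHQ-9, GAD-7, SF-12 and help-seeking questionnaires are scheduled at T1, T2, T3, T6, T12 and T24. For the MINI suicidality module, footnote b says that the time point "corresponds to the time after T0’ and not T0", so its T12 cannot be earlier than the ordinary one. The outcome sections have collection continue until the end of the intervention.
- **Recruitment.** Trial status puts the launch in April 2018 and says of users that "the recruitment of potential users of the StopBlues program is taking place until March 2020".
- **Control arm.** Study design: "After a 12-month post-randomization period, clusters from the control group will be allowed for a further 12-month period to launch their promotional campaign". The section on the intervention to be evaluated says that "the local authorities of the control group will be offered a more sustained promotion at 12 months". The support is greater than arms 2 and 3 received.
- **Analysis.** Statistical considerations: user-level outcomes go into mixed-model repeated-measures analyses, of which the article says "This method will enable the inclusion of all users regardless of their level of adherence to the program". Adjustment is for initial psychological distress and demographics, with random effects for local authorities. No calendar window, period term or promotion-status term is given.

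By contrast, the primary outcome is confined to the 12 months after the start of the intervention, and the control arm's later promotion has its own evaluation on suicides and suicide attempts.

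**The concern.** Secondary objectives 3 and 4 ask whether local promotion changes help-seeking and psychological impairment among users. For the two contrasts with control, that requires control data collected while control areas are unpromoted. That period is fixed on the trial clock and ends around month 12, whereas the questionnaires run on each user's own clock and users keep joining until about month 24.

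If the plan is followed as written, two kinds of control data count as unpromoted when they may not be: all assessments of users who joined in year 2, and the later assessments of users who joined in year 1. The affected share grows with the visit number, so a difference between arms could fade from T1 to T12 simply because the control condition changes. The expected direction is towards no difference, though the sign could reverse if the better-supported later promotion acts more strongly than the first.

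**Working it through.** The article gives no sample size or user numbers for these outcomes, so there is no stated figure to reproduce on this point. The check is calendar arithmetic.

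**Inputs.** Launch is April 2018 (month 0). Recruitment runs to March 2020, so April 2018 to March 2020 inclusive is 24 months. Control promotion is offered at month 12. A user who first connects at month m has visit Tk at month m + k.

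**T12.** With m ≥ 0, visit T12 is at month m + 12 ≥ 12. No control T12 assessment can precede month 12, and T24 falls at month 24 or later. If control promotion starts at month 12, all control T12 assessments fall at or after its start.

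**Later starts.** If a control cluster starts L months after month 12, a year-1 joiner's T12 follows the start when m ≥ L. With uniform uptake in year 1 (assumed) the share is (12 − L)/12:

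- L = 1: 11/12 = 92%
- L = 3: 9/12 = 75%
- L = 6: 6/12 = 50%

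**Earlier visits.** Suppose data are collected to month 24, so that visit Tk exists only for m ≤ 24 − k. It falls after month 12 when m > 12 − k. With uniform uptake over months 0 to 24 (assumed), the share after month 12 is 12/(24 − k) for k up to 12:

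| Visit | Share after month 12 |
|---|---|
| T0 | 12/24 = 50% |
| T1 | 12/23 = 52% |
| T3 | 12/21 = 57% |
| T6 | 12/18 = 67% |
| T12 | 12/12 = 100% |

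**Other uptake patterns, T6.** These are assumptions too.

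- Front-loaded (exponential, mean 6 months): (e⁻¹ − e⁻³)/(1 − e⁻³) = 0.318/0.950 = 33%
- Year-1 joiners only, uniform: 6/12 = 50%
- Uniform over 24 months: 67%
- Uptake three times faster after month 12: (6 × 1 + 6 × 3)/(12 × 1 + 6 × 3) = 24/30 = 80%

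The T6 range is therefore about 33% to 80%.

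**Date discrepancy.** Table 1 gives 22 August 2018 as first enrollment, against the April 2018 launch. If users only joined from August, recruitment lasts about 19 months, but every T12 still falls after month 12. The conclusion does not depend on which date is used.

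**The case against.** The strongest case against the point is that the article is silent here rather than wrong. The quoted phrase is about adherence and missing values and sets no rule on calendar time. Analysis windows are often left to an analysis plan, and none is shown. The article also separates the two periods in places: it gives the initial trial 12 months, says that the sustained promotion is not part of the main intervention, and in the abstract says that it will be assessed with the same outcome measures. A reader could suppose that year-2 control data belong to that assessment.

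Part of this stands. The point cannot rest on the quoted phrase alone. But the article itself fixes the user clock, the recruitment window, the change in the control arm and models that take in all users; together these produce the problem. Where it does separate the periods, in the primary outcome and in the section on the more sustained promotion, it names only suicidal acts. The same post-month-12 control questionnaires could then serve as control data for one objective and as intervention data for another, with no rule to decide.

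Three stronger readings are tempting but unsupported.

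- *Every control T12 assessment is made under promotion.* Control clusters are allowed, and offered, promotion from month 12. Neither word fixes a simultaneous start, and later starts leave some T12 assessments unpromoted.
- *The true effect shrinks by exactly the affected share, to zero at T12.* This needs the later promotion to act fully and at once on users already registered. A control user who joins at month 1 and reaches T12 at month 13 has spent 11 of those 12 months before the offer. The uptake patterns are also assumed.
- *The plan commits to one pooled model with an arm-by-time term.* The article speaks only of mixed-model repeated-measures analyses, without specifying such a model.

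**Conclusion.** The point holds for the user-level questionnaire outcomes compared with control, that is, for secondary objectives 3 and 4 and for the SF-12. As written, control users who join in year 2 are included although promotion has by then been offered in their area, and the scheduled T12 contrast with control largely compares data from promoted periods in both arms. The T12 share is 100% if control promotion starts at month 12. It is 75% or 50% of year-1 joiners' assessments with a delay of 3 or 6 months and uniform year-1 uptake. At T6, about 33% to 80% of control assessments fall after month 12, given data to month 24 and the uptake patterns shown.

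The resulting bias is usually towards no difference. Its size cannot be fixed from the document, because uptake, the actual start dates in control areas and the speed of any effect on existing users are not given.

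A reader might infer that the main trial result is compromised. It is not: the primary outcome is limited to the first 12 months, and neither it nor its sample size is touched. Usage measures taken from software analytics at M12 are not clearly affected either. The matter should be settled before the user-level data are analysed, but it does not threaten the main conclusion.

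**What to change.** For every user-level contrast with control, include only users whose first connection, and only assessments whose date, fall before month 12 after launch. Apply the rule identically in all three arms. Report T12 and T24 between randomized arms as basic versus intensified only. Analyse control-area users and assessments from month 12 onwards under the sustained-promotion objective, and say so there.

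As sensitivity analyses, either restrict by registration date only, or keep all assessments with a time-varying promotion-status term based on each control cluster's actual start date. Both retain more data and would show how much the restriction matters.

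The change is analysis wording only: timing visits from first connection already requires the first-connection and questionnaire dates. The sensitivity term also needs each control cluster's start date. The price is fewer assessments in the control contrast. With uniform uptake in year 1, year-1 joiners would keep 11/12 = 92% of T1, 10/12 = 83% of T2, 9/12 = 75% of T3 and 6/12 = 50% of T6 assessments. There would be no control contrast at T12; if control promotion starts at month 12, no T12 control data from before that start exist to lose.
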